### Goals and hypotheses

The aim of the present study is threefold: (1) to test the effectiveness of OVK within the usual treatment program (OVK + TAU) in reducing symptoms of depression (primary outcome) compared to treatment as usual alone (TAU), (2) to identify mechanisms that can explain program effects (cognitive bias, coping skills), and (3) to test the effects of OVK on secondary outcomes (anxiety, behavioural problems, and therapeutic climate). It is hypothesized that OVK + TAU will be more effective in reducing symptoms of depression in youth than TAU alone, immediately after the program and at three months follow-up. Regarding the explanatory mechanisms, it is hypothesized that OVK + TAU will decrease negative cognitive biases and increase the adequate coping styles. Both of these constructs are expected to mediate the hypothesized effect of OVK on symptoms of depression. Concerning the secondary outcomes, the OVK program is expected to decrease anxiety, since the program contains cognitive and behavioural strategies that are hypothesized to be effective not only for depression, but also for anxiety (e.g., to recognize and challenge threatening interpretations of neutral events, to employ relaxation strategies [23]). A positive effect on behavioural problems is expected, because behavioural problems are believed to be mediated by deficits in internal impulse regulation and poor self-control [24]. If adolescents learn and adopt cognitive techniques to more adequately regulate their levels of anxiety, they will possess a higher level of self-control to regulate their behaviour, eventually leading to a decrease in problem behaviour. Lastly, the responsiveness of group care workers is hypothesized to increase more in the OVK + TAU group than in the TAU group alone. In the TAU+OVK condition, group care workers will be trained in therapeutic skills necessary to correctly implement the program, including listening skills, conversational skills, and techniques to increase group cohesion. These factors are hypothesized to increase the perceived responsiveness of group care workers.

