**Fig. 1 Fig1:**
[figure not shown]
Study design

Randomization will be conducted by an independent statistician of the Radboud University Nijmegen and will take place on the level of the naturally existing treatment groups rather than on the level of individuals (clustered randomization). In the Netherlands, residential treatment groups usually comprise 8–10 adolescents that follow the same treatment program, live in the same building, and are usually taken care of by a permanent staff of nurses and social workers. The benefits of randomisation of natural groups are as follows: (1) it minimizes contamination among adolescents and staff; (2) it best reflects the natural situation in residential treatment settings, increasing the ecological validity of the study; (3) adolescents who will receive the intervention program know each other already and are used to undertake therapeutic activities together; and (4) staff members who will conduct the program already have a therapeutic relationship with the adolescents. Stratification on the cognitive level (MID versus non-MID) will be needed in order to ensure that the cognitive level is evenly distributed across the control and intervention conditions.

To test the effectiveness of the intervention, all adolescents and their parents will complete self-report questionnaires approximately one month before the start of the program and before adolescents know to which condition they are assigned (Baseline, T1), approximately one week before the start of the program (T2), immediately after the program (T3), and three months after the end of the program (T4). Adolescents in the control condition will complete the questionnaires at exactly the same time points. To make sure that all adolescents (MID and non-MID) understand the questionnaires, adolescents will be assisted in filling out the questionnaires by a trained research assistant that is blind to condition.

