### Statistical analyses

The expected effect size for this trial was Cohen’s d = .50. Although in a Dutch study on the effectiveness of OVK among youth with subclinical levels of depression (CDI score >15), the effect size of Cohen’s d = .7 was found [21], we chose a more conservative effect size, because slightly lower levels of depression are expected in our target group, and the effect size is known to be smaller if adolescents have lower baseline levels of depression [17]. An a priori power analysis using G*Power 3.1 [42], for a two-sample *t*-test with a one-sided significance level of 0.05 and equal sample sizes, revealed that a sample size of 102 (51 for each group) is required to obtain a power of .8. To accommodate for the clustering effect, we inflated the sample size with a factor of 1.49 following the suggestions of Campbell et al. [43]. Expecting a drop-out percentage of approximately 20 %, based on the number of adolescents that are expected to be dismissed during the program, the total sample size must be 182 (91 for each group).

All data will be analyzed in accordance with the intent-to-treat (ITT) principle but will also be analyzed separately for the completers only. For the ITT analysis, missing values due to loss of respondents or missing item scores will be handled through multiple imputation using the Markov Chain Monte Carlo method in the statistical package Mplus6 [44]. Missing values will be estimated with logistic regression for categorical variables and ordinary regression for continuous variables.

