The hypotheses will be tested with mixed effects linear regression analyses in Mplus6. Because adolescents are nested within groups and groups are nested within locations, a three-level analysis is most appropriate to account for the non-independence of the data. However, this technique requires relatively large numbers of clusters (~25) and members in clusters (~25) [45]. With 3 locations, 20 clusters, and 8–10 members in each cluster, a multilevel analysis is not suited. To correct for the problem of the potential non-independence of the data for the clusters, the TYPE = COMPLEX procedure in Mplus will be used. This procedure corrects the standard errors of the parameter estimates for dependency. These standard errors are unbiased estimates and will be greater in comparison to the standard errors derived from individual level analysis. The effect of location will be tested by introducing dummy variables in the regression equation. We will check for possible baseline differences between the two conditions in background variables (e.g., age, sex, and ethnic background, cognitive capacities) and depressive symptoms. These variables will be entered as covariates in the regression equation.

To explore the mediating role of adolescents’ cognitive styles, coping styles, and therapeutic climate, mediation analyses will be performed using Mplus. The significance of indirect paths will be tested via bootstrap sampling. Moderating effects of age, gender, and treatment setting on the relation between depression and anxiety will be explored by entering the moderating variables as predictors for depression/anxiety. The moderation and mediation analyses will be done for the OVK and TAU conditions separately. Reporting of the results of the study will be in accordance with the CONSORT statement [46].

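### The bootstrap test of the indirect paths names no resampling unit, and the plan's clustering correction does not reach it; if adolescents are resampled, the test is too liberal under one important null

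*Protocol article*

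**What the plan says.** The Design section randomises existing treatment groups, not individual adolescents. Participants and procedure counts 20 eligible groups of 8–10.

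Statistical analyses first sets multilevel modelling aside: "With 3 locations, 20 clusters, and 8–10 members in each cluster, a multilevel analysis is not suited". It then gives its remedy: "To correct for the problem of the potential non-independence of the data for the clusters, the TYPE = COMPLEX procedure in Mplus will be used". It describes what the remedy does: "This procedure corrects the standard errors of the parameter estimates for dependency".

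The next paragraph turns to mechanisms: "To explore the mediating role of adolescents’ cognitive styles, coping styles, and therapeutic climate, mediation analyses will be performed using Mplus". The test follows: "The significance of indirect paths will be tested via bootstrap sampling". No resampling unit is given, and TYPE = COMPLEX is not mentioned again. The same paragraph then says that the mediation analyses are run in the OVK and TAU conditions separately.

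Goals and hypotheses makes mechanisms the second aim. Of cognitive biases and coping styles it says: "Both of these constructs are expected to mediate the hypothesized effect of OVK on symptoms of depression".

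**The concern.** The hypothesis concerns an indirect effect of condition, so its first link is the condition-to-mediator path. In this trial that path contrasts about 10 groups with 10 groups. A bootstrap interval is read off the resampled estimates, so its width depends on what is resampled. Standard errors corrected elsewhere do not enter it. Drawing adolescents one at a time would reproduce the sampling variation of about 180 independently randomised individuals and understate the variation of a contrast between groups.

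At stake is the second aim. Chance differences between the groups in the two arms could be reported as mechanisms by which OVK works. The risk grows with how alike members of a group are on the mediator. Therapeutic climate is the most exposed candidate, because members of a group rate the same staff.

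**Working it through.** **Inputs from the protocol article.** 20 groups of 8–10; clustering factor 1.49; sample-size chain 102 → 182. The factor can be checked in that chain: 102 × 1.49 = 151.98, and 151.98 × 1.2 = 182.4, which matches the stated 182. No ICC is given for any mediator, and no error rate is given for the mediation test.

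**Assumptions.** Two-sided 5% test; percentile bootstrap; adolescents resampled individually; both arms in one model with condition as predictor; no location dummies or baseline covariates.

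**Implied ICC.** From 1.49 = 1 + (m − 1) × ICC, ICC = .49/(m − 1): .070 for m = 8, .061 for m = 9, .054 for m = 10. The factor was set for the sample size; applying it to a mediator is an assumption.

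**Closed form for the condition-to-mediator path when groups are ignored.** Error = 2 × (1 − Φ(1.96/√DE)), with DE = 1 + (m − 1) × ICC.
- DE = 1.49: 1.96/1.221 = 1.606, error 10.8%. The one-sided 5% analogue, 1 − Φ(1.645/√1.49), is 8.9%.
- m = 9, ICC .10: DE = 1.8, error 14.4%.
- m = 9, ICC .20: DE = 2.6, error 22.4%.
- m = 9, ICC .30: DE = 3.4, error 28.8%.

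**Simulation of the indirect effect.** 20 groups of 9, 10 per arm; condition-to-mediator path zero; mediator–outcome slope .3 or .5; residual outcome ICC about .06; 1,500–2,000 trials per setting with 600 resamples. Rejection rates at nominal 5%:

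| Mediator ICC | Adolescents resampled | Whole groups resampled within condition |
|---|---|---|
| 0 | 5.5–6.7% | 7–10% |
| about .06 | 10–13% | 7–10% |
| .10 | 15–16% | 7–10% |
| .20 | 21–25% | 7–10% |
| .30 | 29–31% | 7–10% |

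A Monte Carlo interval for the product of the two paths, with group-level standard errors and t draws on 20 − 2 = 18 degrees of freedom, rejected in about 4–6% throughout. With 7 per group, to reflect drop-out, resampling adolescents gave 9–10% at ICC .06, 19% at .20 and 24–25% at .30.

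**Other nulls, adolescents resampled, ICC .061.**
- Slope .15, no condition-to-mediator effect: 4.3%.
- Both paths zero: 0.4%.
- Condition-to-mediator effect .5, slope zero: 4.7%. At mediator ICC .20–.30 the same null gives 5.1–6.0%.

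**Separate-arm analysis as written.** Condition is constant within an arm, so there is no condition-to-mediator path. With 10 groups and an individual-level predictor in its place (assumed ICC .06), one path null, resampling adolescents gave 6.6–7.4% and resampling groups 8.8–10.2%. Across the simulations the range is about 6–11%.

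**The case against.** The strongest reply is that the article is silent on the resampling unit, not wrong about it. A condensed article commonly leaves the unit, the number of draws and the interval type to a fuller document. TYPE = COMPLEX is introduced for testing the hypotheses in general, and mediation is one of them. This stands in part: individual resampling is a reading, not something the plan states. It does not dispose of the point, because the article does choose both the correction and the test. As it describes them, the correction acts on a quantity that the test does not use.

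A reader might infer something stronger: that the plan ignores clustering in mediation and so declares mechanisms about twice as often as it should, or four to six times as often for therapeutic climate. The documents do not support that.
- The multiples need a null condition-to-mediator path and a clear mediator–outcome slope; under other nulls the error is near or below 5%.
- The higher multiple needs a climate ICC of .2–.3, which the article does not give; at .10 it is about three times.
- Climate is not among the mediators named under the second aim or under Mediators; it appears as a mediator only in an exploratory sentence in Statistical analyses.
- The multiples arise from a path that the separate-arm analysis does not contain.
- Some of the excess is not due to clustering, since the bootstrap gives 5.5–6.7% at ICC zero.

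These limits all stand. Against them, the null that drives the figures, a mediator that matters for depression but is not moved by OVK, is a central one for the second aim. Correcting the separate-arm sentence alone would also bring the problem into play.

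**Conclusion.** The point holds in a conditional form. The plan leaves the bootstrap's resampling unit open, and its stated clustering correction does not carry over to that test. If adolescents are resampled and condition is in the model, the error under the null just described is about 10–13% instead of 5% at the implied ICC of about .06. It is roughly 20–30% only under an assumed mediator ICC of .2–.3. With a weak or zero slope there is little or no inflation, and in the separate-arm analysis as written the error is about 6–11%. The figures rest on equal-sized groups, a two-sided percentile interval and no covariates. The issue affects the mechanisms aim and not the primary comparison, and it should be corrected before the mediation results are interpreted.

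**What to change.** Replace the bootstrap sentence with one to this effect: indirect effects of condition will be tested, with both conditions in one model, by a Monte Carlo confidence interval for the product of the condition-to-mediator and mediator-to-outcome paths, using standard errors that account for the treatment groups and a t reference with about 18 degrees of freedom.

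If a bootstrap is preferred, state that whole treatment groups are resampled within condition and that with 20 groups the test remains somewhat liberal (7–10%). At the implied ICC this gains only a little over resampling adolescents (9.1% against 12.1% at slope .5), so the Monte Carlo interval is the better choice.

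In either case, reconcile the sentence that runs mediation separately in OVK and TAU. A condition-to-mediator path cannot be estimated within one arm, and the new wording would otherwise contradict it. Any within-arm analysis that is kept should be described as answering a different question.

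The cost is a few sentences and a few lines of code, with no new data. The downside is wider intervals for the indirect effects.

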## Discussion

This study protocol presents a randomised controlled trial testing the effectiveness of an adapted version of the newly developed intervention program OVK on depressive symptoms. The program is based on the PRP-program [17] and is specifically adapted to youth with complex problems in a residential setting and with a parallel version for youth with MID. This target group often shows elevated levels of depressive symptoms or is at high risk for the development of depression. The three main goals of the study are to test the effectiveness of OVK plus treatment as usual (OVK+TAU) of depression compared to treatment as usual (TAU) only, to identify mechanisms that can explain program effects and to test the effects of OVK on secondary outcomes. It is expected that OVK + TAU will be more effective in reducing symptoms of depression in youth than TAU only, immediately after the program and at three months follow-up. Concerning the explanatory mechanisms, it is hypothesized that OVK + TAU will decrease negative cognitive biases and increase adequate coping styles. Both of these constructs are expected to mediate the hypothesized effect of OVK on the symptoms of anxiety and depression. Secondary outcomes include anxiety, behavioural problems, and group therapeutic climate.

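### Running the mediation analyses separately within each arm cannot estimate the indirect effect of OVK that the second aim asks for

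*Protocol article*

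**What the plan says.** In Goals and hypotheses, the second of three aims is "to identify mechanisms that can explain program effects (cognitive bias, coping skills"). Two hypotheses follow from it. The first concerns the mediators themselves: "it is hypothesized that OVK + TAU will decrease negative cognitive biases and increase the adequate coping styles". The second is the mediation claim: "Both of these constructs are expected to mediate the hypothesized effect of OVK on symptoms of depression". The Discussion repeats it with anxiety added: "Both of these constructs are expected to mediate the hypothesized effect of OVK on the symptoms of anxiety and depression".

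The analysis is set out at the end of Statistical analyses: "To explore the mediating role of adolescents’ cognitive styles, coping styles, and therapeutic climate, mediation analyses will be performed using Mplus". Inference is by resampling: "The significance of indirect paths will be tested via bootstrap sampling". The paragraph describes the moderation analyses and then closes the plan for both: "The moderation and mediation analyses will be done for the OVK and TAU conditions separately".

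Nowhere does the article describe a mediation model on both arms together, a multi-group model that contrasts paths between arms, or some other exposure that varies within an arm.

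**The concern.** Aim and analysis do not fit together. Mediation of the effect of OVK is a between-arm quantity: the programme must shift the mediator relative to TAU, and that shift must carry through to symptoms. An analysis confined to one arm contains no contrast between OVK and TAU, so an indirect path reported from it is not an indirect effect of OVK.

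At stake is the interpretation of one of the three aims. The article counts the study of mediators among its strengths and expects the results to guide later improvement of programmes. A mediator-symptom correlation within the OVK arm could be taken for a mechanism when it carries no information on whether the programme acts that way.

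**Working it through.** **Inputs.** No stated figure in the article carries this point; it rests on how the model is specified. The arm size of 91 comes from Statistical analyses and reproduces as 102 × 1.49 = 151.98, then 151.98 × 1.2 = 182.4, so 182 in total. How the drop-out allowance was applied is a separate matter and does not bear on the argument.

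**Model.** Let X be condition (0 = TAU, 1 = OVK + TAU), M the mediator and Y the depression score:

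- M = a·X + error
- Y = c′·X + b·M + error
- indirect effect of OVK = a·b; total effect = c′ + a·b

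**Step 1: is a estimable?** The design matrix for the first equation is [1, X]. Within TAU, X is 0 for everyone; within OVK, X is 1 for everyone. The rank is 1 in each arm, so a cannot be separated from the intercept. With both arms together the rank is 2 and a is estimable. This step needs no assumption about effect sizes.

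**Step 2: what does the within-arm analysis deliver?** With X fixed, a and c′ enter only through the intercepts. The slope of Y on M within an arm is b, whatever a and c′ are.

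**Step 3: does that matter in practice?** Two scenarios with the same total effect were simulated (2,000 runs each, 91 per arm, unit error variances, no clustering). The values of a, b and c′ are illustrative assumptions; the article gives none for the mediators, and its own expectation ("The expected effect size for this trial was Cohen’s d = .50") concerns depression.

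| | Full mediation | No mediation |
|---|---|---|
| a, b, c′ | -0.5, 0.5, 0 | 0, 0.5, -0.25 |
| Total effect c′ + a·b | 0 + (-0.5)(0.5) = -0.25 | -0.25 + (0)(0.5) = -0.25 |
| True indirect effect a·b | -0.25 | 0 |
| Slope within TAU (mean estimate) | 0.499 | 0.500 |
| Slope within OVK (mean estimate) | 0.498 | 0.495 |
| Indirect effect, both arms together (mean estimate) | -0.251 | 0.000 |

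The arm-specific results are practically identical in the two scenarios. The joint model separates them.

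**The case against.** Four things can be said for the plan.

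*The main regressions cover part of the aim.* Statistical analyses says that the hypotheses are tested by regression with cluster-corrected standard errors, and an effect of OVK on the mediators is one of the stated hypotheses. A between-arm test of each mediator is therefore reasonably read as planned. This stands. A reader might infer that nothing in aim 2 can be answered; the article does not support that. A null effect on the mediators would presumably be reported beside the within-arm associations. But that test supplies path a alone, not the indirect effect or its interval.

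*Separately may mean a multi-group model.* Such a model, with means compared across arms, could recover the indirect effect. The article names no such model and no contrast between arms. If it was intended, the sentence still has to say so.

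*Mediation is exploratory.* The analysis paragraph does use that language, while Goals and hypotheses lists mechanisms as an aim with directional hypotheses. Either way, the quantity explored has to be estimable.

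*The bootstrap.* A reader might infer that it will resample individuals and so ignore the group randomisation. The article does not state the resampling unit, and it commits to correcting for clustering in the main regressions; this is a detail that a fuller plan may settle. Nor can the sample-size inflation factor of 1.49 be used to size such an error, since it was set for the depression comparison and the article gives no clustering figure for the mediators.

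**Conclusion.** The point holds in a limited form. The mediation analysis as written cannot estimate the effect of OVK that runs through cognitive or coping styles, and it yields the same within-arm associations whether or not that effect exists. The non-identifiability is algebraic; the simulation only illustrates it, under assumed effects and without clustering.

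The between-arm effect on each mediator remains testable, and the primary comparison on the CDI-2 is untouched. The defect lies in the planned analysis, not in the data, so it can be repaired. A reader might also extend the criticism to the moderation half of the same sentence. The argument here does not reach that far: those analyses are described as concerning the relation between depression and anxiety, where condition is not the exposure.

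Even the repaired analysis rests on an assumption that randomisation does not secure, namely no unmeasured confounding between mediator and outcome. That should be stated when the result is reported.

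**What to change.** 1. Remove mediation from the closing sentence on separate analyses and leave the moderation rule as it is.
2. Fit one mediation model in all randomised adolescents, with condition as the exposure. A natural choice is the mediator at T3 and the CDI-2 at T4, so that the mediator precedes the outcome.
3. Adjust mediator and outcome each for its own pre-programme value. The Design section speaks of questionnaires at T1 in general, but Participants and procedure names only the CDI-2 at T1. If the mediators were measured at T1, use T1; otherwise use T2, noting that T2 precedes the programme but follows allocation and staff training. That order matters most for therapeutic climate, which the training itself is expected to change.
4. Test the product of paths with a method that respects the treatment groups, for example a Monte Carlo interval from the cluster-corrected estimates. State that there are only 20 groups, so the interval should be read with caution.
5. If the mediator-outcome path may differ between arms, add a condition × mediator term to the joint model. Arm-specific slopes can then be shown as supplementary.

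The cost is analysis wording. No added visit or instrument is needed, provided the mediators are measured at T1 or T2 and at T3.
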